#### Healthcare professionals (HCPs)

All HCPs of the following professions working at the study sites or in collaboration with them and involved in the care of the population under study were invited for study participation: physicians, registered nurses, health care assistants, psychologists, social workers, physical therapists, occupational therapists, nutritionists, pastoral workers, logo therapists, social pedagogues, remedial teachers and certified social care workers. To ensure their involvement in PPC, the following inclusion criteria were defined: 1) having cared for patients and their families in the PC phase during a minimum of ten shifts (day/late-shift) or ten consultations and/or 2) having cared for a minimum of two patients in the end-of-life phase and their families or after the death of the child; 3) employment in their institution for a minimum of 3 months. Members of the SPPC team at the intervention site were excluded due to their specialisation and dedicated SPPC activities including intervention provision.

Recruitment took place in two cycles: first cycle beginning of 2021 and second cycle beginning of 2022. All HCPs were invited via the written study information which they received through a local coordinator at their institution. The HCPs were instructed to autonomously check their eligibility for study participation based on the criteria listed above.

### Intervention and comparison

The service of a SPPC team is considered as a complex intervention with components on various levels and of variable dosing, based on the needs of each individual patient and her/his family. All services provided to patients/families by a member of the multiprofessional SPPC team at the University Children’s Hospital in Zurich are considered as study intervention. This includes direct medical, nursing, social, and psychological and spiritual consultations of the patient/family, as well as patient−/family-related consultation of the frontline care team. Bereavement support, as integrated part of SPPC is routinely offered at the individual or group level as appropriate for parents and siblings. The programme at the intervention site offers full 24/7 services from the SPPC team’s physicians, nurses and psychologists and includes home visits.

For patients/families in the comparison group (Aarau, Basel, Berne) routine care is provided as per established paediatric standards in a generalised PPC environment (provided by disease specific specialists with some PPC training [3]) already in place at all study sites. In all of the three comparison sites a PPC team is available since 2019/2020. However, these developing teams differ on the level of capacity, i.e. few human resources and mostly professionals with basic training and experience in PPC without being fully engaged in PPC, no 24/7 coverage, and limited psychologist and bereavement support.

Assignment to study groups will happen naturally, determined through the recruiting study sites. As this study is conducted in a natural environment with continuous development of care practices, adaptations of care structures and processes at all study sites are possible and probable during the duration of the study. No restraints of this natural evolution will be superimposed by the study. Care context is assessed on yearly basis in all four participating study sites, described and used as instrumental variables estimation as applicable.

### Outcomes and procedures

Improving and maintaining QOL is the core intention of PC and is the main outcome of this comparative effectiveness study. For an overview of the study’s setup and timeline, outcomes and measurements, and assessment timepoints see Fig. 1 and Tables 1 and 2.

**Table 1 Tab1:** Overview of outcomes, measurements and data collection time points

	Data source / Instrument	Domains / Dimensions	Data Collection
**Clinical Outcomes:**			
**Primary outcome:**			
Caregiver QOL	Quality of Life in Life Threatening Illness–Family Carer Version (**QOLLTI-F**): 16 items [27]	State of carer, patient wellbeing, quality of care, outlook, environment, finances, and relationships	Baseline at study entry and dynamically after that. Self-report. Mothers, fathers
**Secondary outcomes during the child’s PC phase:**			
Child’s QOL	DISABKIDS Chronic Generic Measure - **DCGM-37**: 37 items [28]	Mental, social, and physical, based on the WHO conceptualisation of health-related QOL.	Baseline at study entry and dynamically after that. Self-report (7 years and older) or proxy report (parent).
Child’s symptoms	Memorial Symptom Assessment Scale (**MSAS**): 30 or 8 items (depending on child’s age) [29, 30]	Prevalence, severity, distress	
Siblings QOL	KIDSSCREEN-27: 27 items [31]	Physical well-being, psychological well-being, autonomy & parent relation, peers & social support, school environment	Baseline at study entry and dynamically after that. Self-report (8 years and older)
Professional’s QOL	Professional QOL (**ProQOL**): 30 items [32]	Compassion satisfaction, compassion fatigue, i.e. burnout and work-related secondary trauma	Cross-sectional. Self-report. HCPs not specialised in PPC but **involved in direct patient care of PPC patients**.
**Secondary outcomes during bereavement:**			
Grief processes	Würzburger Trauerinventar” (**WüTi**): 24 items [33]	Acute emotional and cognitive impairments, general personal development/growth, feelings of guilt and self-reproaches, increase of sensitivity/empathy for others, closeness to the late person	1 month after the child’s death and three-monthly after that. Self-report. Mothers, fathers
Parental QOL	The WHO Quality of Life (**WHOQOL-BREF**): 26 items [34]	Physical, psychological, social relationships, environment	
Siblings QOL	KIDSSCREEN-27: 27 items [31]	Physical well-being, psychological well-being, autonomy & parent relation, peers & social support, school environment	1 month after the sibling’s death and three-monthly after that. Self-report (8 years and older).
**Mediators of SPPC Outcomes:**			
Sense of coherence (SOC)	Family Sense of Coherence (**FSOC**): 26 items [21]	Comprehensibility, manageability, meaningfulness	Cross-sectional at study enrolment. Structured interview. Mothers, fathers
Family hardiness (FH)	Family Hardiness Index (**FHI**): 20 items [22]	Commitment (internal strengths and cooperativeness), challenge (resourcefulness and willingness to learn), control (sense of having control over life circumstances)	Cross-sectional at study enrolment. Structured interview. Mothers, fathers
**Service Outcomes:**			
Healthcare resource utilisation	Routine data	Number of hospital admissions including number of emergency and/or outpatient consultations and number of admissions to a paediatric intensive care unit (PICU), number of resuscitations, number of invasive procedures e.g. surgery and imaging requiring sedation, total length of hospital stay (LOS) per admission, number of days receiving professional community home care services	Chart review, continuously during the child’s PC phase.
Place of death	Routine data	PICU, hospital ward, home, and other	Chart review at time of death
**Economic outcomes:**			
Economic analysis	Routine data Household data	Costs related to healthcare resources utilised Effective costs charged and paid by formal payers Direct and indirect health-related household expenditures: Out of pocket payments, changes in employment status and income, financial support	Cost data retrieved from hospitals and formal payers for the time of study participation. Baseline at study entry and dynamically after that. Self-report. Mothers, fathers
**Introduction of SPPC:**			
Introduction of SPPC and Validation of the PaPaS-Scale	Paediatric Palliative Screening Scale (**PaPaS-Scale**): 11 items [25]	Trajectory of disease and impact on daily activities of the child, expected outcome of treatment directed at the disease and burden of treatment, symptom and problem burden, preferences/needs of patient or parents / preferences of HCPs, estimated life expectancy	Cross-sectional for each family and child older than 1 year of age at study entry.
**HCPs Outcomes**			
Professional Quality of Life	ProQOL Version 5: 30 items [35]	Compassion fatigue, i.e. burnout and secondary traumatic stress, and compassion satisfaction	Cross-sectional. Self-report. HCPs not specialised in PPC and involved in direct care of PPC or end-of-life patients.

**Table 2 Tab2:** Study visits and assessments

Study Periods	Care Timepoint									Bereavement Timepoint				
Timepoint^**a**^	Screening/ Baseline	CT1	CT2	CT3	CT4	CT5	CT6	CT7	CT8	Death of child	BT1	BT2	BT3	BT4
Time interval in days (Reference = 0)	0	15	30	60	90	120	150	240	330	0	30	120	210	300
Informed Consent / Demographic Data	**x**													
Inclusion / Exclusion Criteria	**x**													
Introduction of SPPC (PaPaS-Scale)	**x**													
Sense of coherence (FSOC)	**x**													
Family hardiness (FHI)	**x**													
Caregiver QOL (QOLLTI-F)	**x**	**x**	**x**	**x**	**x**	**x**	**x**	**x**	**x**					
Child’s QOL (disabkids)	**x**		**x**	**x**	**x**	**x**	**x**	**x**	**x**					
Child’s symptoms (MSAS)	**x**	**x**	**x**	**x**	**x**	**x**	**x**	**x**	**x**					
Siblings QOL (KIDSSCREEN-27)	**x**	**x**	**x**	**x**	**x**	**x**	**x**	**x**	**x**					
Healthcare resource utilisation and costs		**x**	**x**	**x**	**x**	**x**	**x**	**x**	**x**	**x**				
Direct and indirect health-related expenditure	**x**		**x**	**x**	**x**	**x**	**x**	**x**	**x**			**x**		**x**
Professional’s QOL (ProQOL)									**x**^**b**^					
Place of death										**x**				
Grief processes (WüTi)											**x**	**x**	**x**	**x**
Parental QOL (WHOQOL-BREF)											**x**	**x**	**x**	**x**
Siblings QOL (KIDSSCREEN-27)											**x**	**x**	**x**	**x**

^a^The timeframe to complete the questionnaire is 1 week

^b^Professional’s QOL will be assessed after the first year of recruitment and after the second year, i.e. end of recruitment phase

#### Patients and families

Since a large proportion of the study population is young or cognitively impaired, we defined caregiver QOL as the primary outcome. Each participating patient/family is followed for a maximum time of 1 year as long as the child is alive. Assessment timepoints are dynamic, starting with two bi-weekly assessments, followed by four monthly assessments and three-monthly after that. For families, who lose their child during the study, bereavement follow-up continues for another year with four assessments. All outcomes on the family level are assessed as surveys with self-reported and validated questionnaires on paper. Questionnaires are distributed in the hospital or sent home by the study team in case the child is at home at the time of a study assessment. Outcomes on the patient level are assessed as proxy measures through the parents, unless the patient is capable to report her−/himself. Siblings’ QOL is only assessed, if they are able to self-report.

Service outcomes are assessed through the collection of routine data via chart review at assessment timepoints. This includes patient-specific information related to healthcare resource utilization, e.g. hospital admissions and length of stays, procedures, and diagnostic information and date of death. Economic outcomes are assessed through queries for each patient for costs on the healthcare system level (hospitals, formal payers) and through self-reported direct and indirect health-related expenditure data (questionnaire) from participating families.

#### HCPs

HCPs’ professional QOL was retrospectively assessed for 1 year back after the first and second study year. All HCPs who returned their informed consent received the questionnaire as a hard copy through institutional or postal mail.

All study participants are withdrawn from the study in the case of consent withdrawal or relevant non-adherence to study procedures, i.e. failure to complete questionnaires. No specific follow-up beyond the date of withdrawal/discontinuation is performed and no more data is collected. All data collected up to study withdrawal/discontinuation will be considered for analysis.

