#### Primary and secondary analyses

The primary outcome QOLLTI-F of the care-giving parents 1 month after study inclusion will be analysed by a linear mixed-effects model with QOLLTI-F at baseline and group (SPPC vs. comparison) as fixed effects. A random intercept will be modelled per patient (to account for the non-independence of parents from the same patient). In addition, all measurements of QOLLTI-F taken at different follow-up visits will be analysed by a linear mixed-effects model as above, but with an additional random intercept per parent (to additionally account for the non-independence of multiple measurements per parent).

To adjust the effect size estimate for SPPC vs. comparison for potential confounders, we will use propensity score weighting. Potential confounders were already identified and include characteristics of the patient (diagnosis, age, sex), disease duration, family system (sense of coherence, family hardiness), sociodemographic variables of the family (e.g. parental living situation, family income), and contextual information (e.g. study site characteristics). As a sensitivity analysis, we will add the most important confounders as covariates in the statistical models (analysis of covariance approach).

Secondary endpoints will be analysed by linear mixed-effects models or generalised linear mixed-effects models (in case of non-normal error distribution). Normal linear models or generalised linear models may be used for secondary outcomes measured only once per patient. Sensitivity analyses will be performed as applicable and appropriate.

Missing measurements of the primary outcome, QOLLTI-F at 1 month, will be multiply imputed, based on measurements taken at 2 weeks (first follow-up measurement) and available patient characteristics.

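### Families who stop completing questionnaires are withdrawn as if consent had been withdrawn, which cuts off chart, cost and place-of-death data that need no questionnaire

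*Protocol article*

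**What the plan says.** The withdrawal rule is in Methods, Outcomes and procedures, at the end of the HCPs subsection. Despite that heading it covers everyone: "All study participants are withdrawn from the study in the case of consent withdrawal or relevant non-adherence to study procedures, i.e. failure to complete questionnaires". The second of these triggers, "relevant non-adherence to study procedures, i.e. failure to complete questionnaires", is the one at issue. The consequence is the same for both reasons: "No specific follow-up beyond the date of withdrawal/discontinuation is performed and no more data is collected". Earlier data are kept: "All data collected up to study withdrawal/discontinuation will be considered for analysis".

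Other parts of the article show which outcomes need a questionnaire and which do not:

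- Patients and families subsection: "Service outcomes are assessed through the collection of routine data via chart review at assessment timepoints". Date of death is among the items collected this way.
- Table 1, Service Outcomes, place of death: "Chart review at time of death".
- Table 1, Economic outcomes: "Cost data retrieved from hospitals and formal payers for the time of study participation".
- Primary and secondary analyses: missing 1-month QOLLTI-F scores "will be multiply imputed, based on measurements taken at 2 weeks (first follow-up measurement) and available patient characteristics". All follow-up QOLLTI-F measurements also enter a longitudinal mixed model.

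**The concern.** Two different events lead to the same result. Withdrawn consent can oblige the study to stop collecting. Unreturned forms mean only that the questionnaire data are missing. Under the rule, a family that has not withdrawn consent but has stopped returning forms also disappears from chart review, the cost window and the record of where the child died.

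Whether the programme reduces use of healthcare resources and costs is a named objective. Use, cost and place of death all turn on the last phase of the child's life, and it is reasonable to expect families to return fewer forms then. The data most likely to be cut off would therefore be those that matter most for these outcomes. The groups are different hospitals with different staffing, so the loss need not be equal between them.

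**Working it through.** **1. Any planned figure.** The article gives no expected rate of withdrawal for non-completion. Its only allowance, the 10% drop-out in the sample size section, counts deaths and withdrawn consent before any QOLLTI-F assessment. There is no figure of the plan's own to reproduce on this point.

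**2. What stops, and whether it needed a form.**

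| Outcome | Source in the article | Needs a family questionnaire? | After withdrawal for non-completion |
|---|---|---|---|
| Admissions, PICU, procedures, length of stay | Chart review | No | Stops |
| Place of death | Chart review at death | No | Lost entirely if death comes later |
| Hospital and payer costs | Institutional and payer records | No | Window closes, as it is tied to study participation |
| Later QOLLTI-F | Parent form | Yes | No longer collected |
| Bereavement outcomes | Parent and sibling forms, four timepoints | Yes | Never starts if death comes later |

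The first three rows are avoidable loss. The last two may be avoidable, because a family that misses some forms may return later ones.

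**3. Size per withdrawn family.** Table 2 places care-phase assessments at days 0, 15, 30, 60, 90, 120, 150, 240 and 330. For a child alive at day 330 and a family withdrawn at day *w*:

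share of scheduled care-phase time lost = (330 − *w*) / 330

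| Withdrawn at day | Days lost | Share | QOLLTI-F visits still to come |
|---|---|---|---|
| 60 | 270 | 82% | 5 |
| 90 | 240 | 73% | 4 |
| 150 | 180 | 55% | 2 |
| 240 | 90 | 27% | 1 |

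If the child dies before day 330, fewer days are lost, but they include the terminal phase and the place of death.

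**4. When loss would bias a quality-of-life comparison.** This is an illustration, not an estimate for this study. From the sample size section: means 6 (SPPC) and 5 (comparison), SD 1.7, true difference 1.0. Assumed: the loss rates, and the link of loss to the score *y*,

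P(lost) = 1 / (1 + exp(−(a − s(y − 5.5))))

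with s = 0.3 or 0.6 per point and a set in each group to give the stated loss. The estimate uses observed cases at one timepoint, with no imputation or covariates.

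| Loss, comparison / SPPC | Estimate, s = 0.3 | Estimate, s = 0.6 |
|---|---|---|
| 10% / 10%, 20% / 20% or 30% / 30% | about 1.00 | about 1.00 |
| 20% / 10% | 0.92 | 0.86 |
| 30% / 10% | 0.84 | 0.72 |
| 10% / 20% | 1.09 | 1.15 |
| 10% / 30% | 1.16 | 1.27 |

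With s = 0 every combination gives about 1.0. In this model, bias in the difference needs loss that depends on quality of life and also differs between groups, and it can go either way. The article reports neither condition.

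**The case against.** The strongest reply is that the rule is milder than it looks, and most of this stands.

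- **One missed form.** A reader might infer that a single missed questionnaire means permanent exit. The rule speaks of relevant non-adherence, and the plan imputes missing 1-month scores, so it does not treat every gap as withdrawal. The threshold is not given, but a condensed article may leave that to the full protocol. Wherever the threshold lies, the consequence for chart and cost data is the same.
- **Power.** A reader might attach a power loss to the rule. The documents do not support one. Only baseline and day 15 precede the 1-month form, and a parent who does not return that form lacks the score whether or not the family is withdrawn. Any figure would rest on an invented rate and would mostly measure non-response.
- **Imputation.** A reader might say that the rule weakens the planned imputation by removing later scores. The stated imputation uses the 2-week score and patient characteristics, so later scores matter to the longitudinal model only.
- **Bias.** The longitudinal mixed model uses all available measurements and is valid if data are missing at random. Differential loss is not documented. Recruitment by SPPC staff at the intervention site does not establish it, since the study team sends questionnaires to families at home.
- **Consent.** The consent documents are not available here, so it cannot be seen whether chart and payer access was agreed beyond discontinuation. The fair wording is that no reason is stated, not that none exists.

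None of this explains why collection that needs nothing from the family should stop while consent stands.

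**Conclusion.** The point holds in a limited form. As written, the rule treats non-completion of questionnaires like withdrawn consent, and so truncates utilisation, cost and place-of-death data for families who have not withdrawn consent. It also ends their later QOLLTI-F scores and any bereavement follow-up. This follows from the text alone.

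The loss for one withdrawn family can be most of the care phase: 82% of scheduled time at day 60 and 55% at day 150, assuming the child is alive at day 330. The number of such families is unknown, so no study-wide size can be given and no power figure belongs with this point.

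Bias in the service, cost and longitudinal comparisons is a plausible risk if non-completion tracks the child's deterioration and differs between sites. It should not be stated as a fact. The 1-month primary endpoint is little affected by the rule itself.

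**What to change.** Amend the withdrawal paragraph so that stopping questionnaires and withdrawing consent are separate events:

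1. Treat an uncompleted questionnaire as missing at that visit. Keep offering later ones, including in bereavement, unless the family declines.
2. Reserve full withdrawal, with an end to all collection, for withdrawn consent.
3. For families who no longer complete forms, continue collection of chart, hospital and payer cost, vital-status and place-of-death data, as far as their consent allows. Word the cost window so that non-completion does not close it.
4. For families already removed only for non-completion, collect the same data retrospectively within the limits of their consent.
5. Report by group and site how many families stopped questionnaires, and how many withdrew consent.

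The cost is a small amendment, some extra mailings and some chart abstraction through processes already in place. Recruitment closed in May 2022, so the last 1-month assessments fell around June 2022 and an amendment after that cannot restore them. Data collection runs to May 2023. What can still be gained is in the secondary service and cost outcomes, much of it retrospectively, and in the remaining longitudinal scores.

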### Sample size and statistical analyses

We hypothesise that SPPC positively influences the QOL of the caring parents. The null hypothesis is that QOL does not differ between parents of patients in the SPPC programme and the comparison group. The sample size (number of paediatric patients) was calculated to be able to show a difference of 1 point in the QOLLTI-F score [27] 1 month after study inclusion. The calculations are based on an expected mean QOLLTI-F of 5.5 (on a scale from 0 to 10) and an expected standard deviation of the QOLLTI-F score of 1.7, as reported in Cohen et al. [27]. Note that similar values of mean ± SD, i.e., 5.8 ± 1, were observed by Groh et al. [36].

Sample size was calculated using a resampling method. Each sample size, n i = 1,...,41 = 10, ..., 250, was evaluated by simulating *R* = 499 times the QOLLTI-F of n_i_ individual pairs of care giving parents from a multivariate normal distribution, using a correlation of 0.8 between parents of the same patient. For each sample size n_i_, half of the patients were allocated to the SPPC group and comparison group, with mean QOLLTI-F of 6 and 5, respectively, and a (within group) standard deviation of 1.7. Assuming that only one parent participates in the study for 30% of the patients, this proportion of simulated QOLLTI-F scores for the second parent was omitted, resulting in simulated QOLLTI-F scores for a pair of parents for 70% of the patients, and for only one parent for the remaining 30% of patients. The difference in QOLLTI-F between parents of SPPC vs. comparison patients was then estimated with a linear mixed-effects model with group (SPPC vs. comparison) as fixed factor, modelling a random intercept per patient (to account for the non-independence of parents from the same patient). Sample size was set to ensure at least a power, 1 – β, of 0.8 at a significance level, α, of 0.05.

For this study, a total of 98 paediatric patients should be recruited (i.e., 49 from the SPPC programme and 49 for comparison) to ensure a total of 98 evaluable pairs of care giving parents, considering a drop-out rate (i.e., proportion of patients who died or withdrew informed consent before QOLLTI-F could be assessed at least once) of 10%. Sample size was estimated using R (Version 3.5.0) [37], using the R packages nlme [38] and sse [39].

